## Abstract

**Introduction:**

Symptoms of anxiety and depression in Indian adolescents are common. Schools can be opportune sites for delivery of mental health interventions. India, however, is without a evidence-based and integrated whole-school mental health approach. This article describes the study design for the safeguarding adolescent mental health in India (SAMA) project. The aim of SAMA is to codesign and feasibility test a suite of multicomponent interventions for mental health across the intersecting systems of adolescents, schools, families and their local communities in India.

**Methods and analysis:**

Our project will codesign and feasibility test four interventions to run in parallel in eight schools (three assigned to waitlist) in Bengaluru and Kolar in Karnataka, India. The primary aim is to reduce the prevalence of adolescent anxiety and depression. Codesign of interventions will build on existing evidence and resources. Interventions for adolescents at school will be universal, incorporating curriculum and social components. Interventions for parents and teachers will target mental health literacy, and also for teachers, training in positive behaviour practices. Intervention in the school community will target school climate to improve student mental health literacy and care. Intervention for the wider community will be via adolescent-led films and social media. We will generate intervention cost estimates, test outcome measures and identify pathways to increase policy action on the evidence.

**Ethics and dissemination:**

Ethical approval has been granted by the National Institute of Mental Health Neurosciences Research Ethics Committee (NIMHANS/26th IEC (Behv Sc Div/2020/2021)) and the University of Leeds School of Psychology Research Ethics Committee (PSYC-221). Certain data will be available on a data sharing site. Findings will be disseminated via peer-reviewed journals and conferences.

Strengths and limitations of this studyA key strength of this study is its focus on depression and anxiety prevention, which are common mental health conditions among Indian adolescents.The study uses a public mental health systems approach, which adopts a ‘person-in-context’ perspective and recognises multiple determinants of mental health.Extensive codesign of interventions will promote cultural relevance and acceptability by key stakeholders, including adolescents, teachers, parents and school communities.The COVID-19 pandemic makes this research more pertinent but may affect recruitment of the schools/adolescents or may lead to participation bias if the study processes are conducted online by excluding those with limited access or who lack technical skills.The opt-in approach to consent may lead to participation bias.

## Introduction

Mental health conditions including depression and anxiety disorders are among the top 10 causes of illness and disability in adolescents.^1^ Half of all lifelong mental health conditions have their onset in adolescence.^2^ Poor mental health in adolescence is associated with poor physical health and lifelong disadvantage, especially if education is disrupted, impacting occupational and social trajectories.^3^

India has the largest adolescent population in the world (253 million).^4^ An estimated 9.8 million Indian aged 13–17 year olds (pooled prevalence of 7.3%) have a clinical mental health condition^5^ but levels seem considerably higher in urban areas and among school-going adolescents.^6^ Although there are limited data on the treatment gap in adolescents, the overall treatment gap for mental disorders in India is around 90%.^5^ The treatment gap and the effectiveness and cost-effectiveness of early intervention are driving investment into public mental health in efforts to develop scalable programmes that can reach adolescents before their symptoms progress to levels of a clinical disorder.^5^ Tackling preventable and treatable health conditions, and improving the quality of education for adolescents, present the single best investments for health and well-being a low-income and middle-income country (LMIC) can make.^7^

Schools have tremendous potential as platforms for public mental health interventions, which can secure positive effects on mental health, including a reduction in anxiety and depression, and which can be delivered, sustained and scaled in LMICs.^7^ School provision can increase access to interventions over and above existing mental healthcare systems, which in LMICs, are typically fragmented, under-resourced and not tailored to adolescents.^8–10^ Improving school experience may also promote longer participation in education, which reduces a number of risks for girls in particular.^8^ The Lancet commission on adolescent well-being calls for investment in school mental health, bolstered by the rise in school attendance^8^ including in India (97% enrolment).^11^ Although some adolescent mental health programmes exist in India, there is as yet no integrated, evidence-based, whole-school mental health approach for adolescents.

Our project responds to this need by identifying existing school interventions, which can be integrated, tailored and culturally adapted into a systems approach^12^ in India through a process of coproduction with stakeholders. Given the multiple determinants of adolescent mental health in India,^5^ interventions will need to target individual and contextual factors. In India, a key contextual determinant of adolescent mental health is the nature of schooling, including the use of corporal punishment,^13–15^ extreme academic pressure,^16 17^ a lack of mental health literacy among adolescents, teachers and parents,^18–20^ prevailing mental health stigma and bullying,^21^ poorly supported staff, often with large class sizes and a lack of mental health support within schools.^22^ Although the Government of India endorsed the WHO Health Promoting School model (2007),^23^ progress on school mental health has been slow. To date, school initiatives in India have mostly targeted physical health and life skills.^24–27^ There is an urgent need to accelerate improvements in mental health in Indian schools, from a safety and rights perspective,^28^ to reduce school risks to adolescent mental health and to improve population health. India has limited evidence-based, scalable school programmes, endorsed by policy, to support adolescent mental health. This is a critical care gap.^5 29^ Our study aims to contribute to the evidence base about what works in Indian schools to support adolescent mental health.

There is some evidence for school-based universal mental interventions for depression and anxiety prevention, and mental health promotion, in high-income countries.^30 31^ The evidence in LMICs is promising though limited.^8–10^ Three whole-school health and life-skills programmes with small mental health components have been tested in India.^24 26 32 33^ One did not report any beneficial clinical outcomes^24^ and one has yet to establish effectiveness,^32^ indicating that life-skills interventions may be insufficient to impact adolescent anxiety and depression. The third is a health promotion programme (multicomponent school health promotion programme (SEHER)) focusing on school climate, and targeting physical and sexual health, bullying, gender equality and depressive symptoms. It focused on promoting adolescents’ social and problem-solving skills, engaging adolescents, teachers, and parents in school-level decision-making and delivering factual knowledge about health and risk behaviours to the school community.^26^ Outcomes were positive, including for depressive symptoms, with benefits extended up to two years.^33^ It did not, however, target anxiety nor include broad mental health promotion. This is a critical gap given the prevalence of anxiety disorders in adolescence and its comorbidity with depression.

Our study, safeguarding adolescent mental health in India (SAMA), builds on learning from SEHER in terms of the value and acceptability of whole-school, multicomponent interventions in Indian schools and the contribution of school climate to adolescent well-being. Project SAMA extends SEHER in several ways. Our health objective is to reduce symptoms of both anxiety and depression in symptomatic adolescents and to promote the well-being all school-going adolescents. We will codesign, and feasibility test, a suite of school interventions in India targeting multiple risks and protective factors across the school system. We extend SEHER by including codesigned interventions targeting teachers and parents, as well as an adolescent mental health psychoeducation intervention. We also augment the school climate intervention of SEHER via coproduction. The SAMA study will take place between January 2021 and December 2023.

## Method and analysis

### Study design

SAMA will run over 36 months and will be delivered via eight work packages (WP) (see figure 1).

**Figure 1 F1:**
[figure not shown]
Study work packages (WP).

WP1–4 are intervention codesign/coadaptation and feasibility studies following Medical Research Council guidance^34^ and the Six Steps in Quality Intervention Development,^35^ targeting adolescents (14–15 years), teachers, the school community and parents (table 1). WP5 is implementation research on these interventions and WP6 is an exploratory cost-effectiveness study of the interventions. WP7 and 8 target policy and local community systems, respectively. Year 1 will focus on codesign and coadaptation of interventions via WP1–5. Years 2 and 3 will include a feasibility study of the adapted interventions alongside WP6 and 7. WP8 will run across all 3 years.

**Table 1 T1:** Intervention aims and requirements defined in advance

WP	Intervention	Requirements defined prior to codesign	Primary outcome	Secondary outcomes (include but not restricted to)
1	Whole-school curriculum adolescent mental health programme	15–16 year olds (grade 9) as advised by schools 6–8-week duration	Symptoms of anxiety and depression	Mental health literacy, stress, self-esteem, resilience, quality of life, school attendance and performance
2	Teacher education programme	Low intensity Suitable for all levels of staff	Teacher mental health literacy	Teacher attitude towards and use of positive behaviour management practices
3	School climate intervention	Up to 6 months	School climate	Mental health literacy, perceived stigma, perceived support
4	Parent mental health literacy intervention	Low intensity	Parent mental health literacy	Requests for more mental health information/support/referrals

SAMA will work with adolescents as partners in all stages of the project. In addition to the adolescents involved as participants in codesign, we will have a Youth Advisory Board who will be consulted on all project components, a subset of whom will form adolescent film crews and drive the social media campaigning (both WP8). We will have three other advisory boards (Steering Group, Scientific Advisory Board, Ethics Oversight Committee).

For WP1-4, some broad interventions requirements have been defined in advance of codesign, including the aims and primary and secondary outcomes. These are shown in table 1. It is possible that codesign discussions may lead to the inclusion of additional outcome measures. All interventions will be delivered by external lay counsellors. Use of lay counsellors can represent effective task-shifting task, an approach endorsed by the WHO in low-resource settings.^36^ Task shifting involves assigning tasks and responsibilities from more specialised to less specialised groups and requires clearly defined roles with effective training and supervision. There is some evidence that this delivery approach is superior and preferred to teacher-delivered interventions, and peer educator programmes, at least for adolescent mental health programmes.^22 26 32^ Notably, the cluster randomised trial of SEHER conducted across 75 schools in Goa was found to be effective when delivered by lay counsellors but not teachers.^26^ There are additional benefits of having a small team of lay counsellors working closely in partnership with schools. These include each lay counsellors having a co-counsellor to work alongside to deliver SAMA, counsellors being able to get to know particular schools well (ie, their systems, culture), having constancy in the lay counsellors so school staff and students can build familiarity and trust, and having a defined conduit for communication about SAMA within schools and between school and the study team.

### School recruitment

We will recruit eight schools in Kolar and Bangalore to participate in both the codesign and feasibility stages of SAMA (WP1–6). School recruitment will be facilitated by the Karnataka State Primary and Secondary Education Ministry and the Karnataka State Secondary School Headmaster’s Association. We will recruit two school types (government and low-cost private) to identify school factors that may affect feasibility. Schools will be eligible to take part in SAMA if they endorse the delivery of WP1–6 in their schools, including participation in codesign. WP1 intervention feasibility testing will be with a new grade 9 cohort not involved in codesign.

### Year 1: codesign/coadaptation of interventions

Codesign will proceed in stages (see figure 2) and will include coadaptation of existing interventions as well as design of new components where needed (eg, content, implementation, safeguarding). We begin with coadapting interventions before identifying the need for new codesigned elements. Our approach to coadaptation is informed by phases 1–3 of the ADAPT model for introducing complex public health interventions into new settings^37^ and also by Perera *et al.*’s approach^38^ to adapting low-intensity psychological interventions into new cultural settings. WP5 runs alongside WP1–4 and aims to identify implementation facilitators and barriers for all intervention components. As well as adapting interventions, we will coproduce with adolescent and stakeholders a whole-school safeguarding protocol tailored to the interventions.

**Figure 2 F2:**
[figure not shown]
Stages of coadaptation/codesign. WP, work packages.

#### Phase 1: exploration of needs and existing interventions

##### Initial assessment

A desk review will be conducted to gather knowledge on the local context and research evidence relevant to our project aims, including identification of any existing best practice and policy requirements. This will feed into an evidence-based, multilevel needs assessment of endusers, families, schools and regional/state systems to sensitise our selection of interventions and implementation approach.

##### Intervention selection and exploration

We aim to identify interventions that are likely to be acceptable, feasible and efficacious in our target context to meet our project aims. We will search for interventions with the potential (after coadaptation) to impact at least the primary outcome for each WP (table 1). As per figure 2, a non-systematic search will be conducted first to collate or identify interventions which are known to the team in India, referenced in Indian education or mental health policies or referenced by Indian or global organisations (eg, Save the Children, WHO). This will be followed by a systematic search. Umbrella review protocols for these are registered on PROSPERO^39–42^ and reviews are nearing completion. Considering search returns from both the non-systematic and systematic searched, WP1–4 leads will propose candidate interventions to be taken to Phase 2. While established effectiveness of an intervention is important, we also need to consider the coherence, integration, implementation and scalability of interventions for the local context.^43^ Proposals will be reviewed by the research team and project advisory boards, which include in-country adolescents, schools and mental health professionals as well as the team which led SEHER.^26^ Amendments to proposals will be made where necessary.

This phase includes work on implementation protocols (WP5). We will build on a UK framework for a whole-school mental health intervention^44^ based on the Consolidated Framework for Implementation Research (CFIR).^45^ The framework will be iteratively developed as SAMA interventions are finalised, drawing on existing implementation evidence from India, including the SEHER study,^26^ and through our coadaptation processes.

#### Phase 2: preparation for codesign

##### Identification of mismatches and model development

Candidate interventions will be assessed against our multilevel needs assessment; those failing to meet significant need will be rejected. We will then develop a model of how the final interventions could work across systems before identifying the aspects (across surface and deep levels^46^), which are most critical to take forward to codesign/coadaptation. Decisions here will be informed by the approach of Perera *et al.*^38^ and their use of the Ecological Validity Model.^47^ This will lead to the generation of adaptation hypotheses, that is, our proposals for which intervention aspects will need to be culturally adapted. The Ecological Validity Model prompts direct consideration of the language, persons, metaphors, content, concepts, goals, methods and context (which includes implementation) of the intervention to be adapted. We will supplement these proposals with codesign needs, that is, new features which need to be created because of the systems approach or local school context. Coadaptation and codesign proposals will be finalised in consultation with our youth and advisory boards.

##### Coadaptation and codesign

Our aim in this stage is to optimise the acceptability, feasibility, efficacy and meaningful evaluation of the suite of interventions by involving endusers and stakeholders in intervention adaptation and its associated implementation approach. We will host codesign/coadaptation workshops for each WP intervention, each involving adolescents (14–16 year olds, single-gendered groups with more females), parents, schools (including teachers and institute heads) and key stakeholders in separate workshops. WP2 codesign will additionally involve national organisations (eg, State Education & Health Department, Teachers of India, ChildLine India, and Save the Children). WP4 codesign will begin with a stakeholder event to identify community-led solutions to reaching parents. Creative evaluation methods will be devised during codesign to be sensitive to low literacy levels, low chance of measure completion and desirability bias. Implementation barriers, facilitators and developing implementation protocol will be a standing item for consultation in codesign workshops. Codesign/coadaptation workshops will include a range of age-appropriate and role-appropriate discussions and activities centering on the coadaptation proposals developed in the previous stage.

#### Phase 3: undertaking modifications

We will modify the interventions based on coadaptation and codesign workshop outputs. We will use the expanded Framework for Reporting Adaptations and Modifications-Expanded (FRAME) approach to report modifications to interventions.^48^ This approach documents when, why and how modifications were made, and differentiates cultural adaptation from adaptations made for other reasons. Proposed modifications will be reviewed by the full team to ensure modified interventions still meet the multilevel needs assessment, retain active ingredients and are coherent as a suite of interventions. Modifications and final prototype interventions will be reviewed by our youth and advisory boards as well as a board of in-country mental health professionals and education sector representatives to ensure they meet state and national requirements. Once finalised, we will produce for each WP intervention a logic model, programme manual, intervention resources, lay counsellor training and supervision protocol, implementation and evaluation protocols.

### Year 2: feasibility testing

Lay counsellors will be from the local areas, have at least a master’s qualification in psychology or a related discipline and experience in working with young people and/or schools. Prior to the launch of the feasibility study, they will receive full training over 3 months by a clinical psychologist on the team, supported by another team member experienced in training lay counsellors. Trainees will deliver multiple mock sessions of intervention delivery to support readiness for delivery in schools and quality control. The feasibility study will run in eight schools, with three randomly assigned to waitlist. The four interventions will run in parallel in schools. Lay counsellors will complete weekly monitoring logs of intervention delivery in each school, including logging of modifications made (as per FRAME^48^) and will have weekly supervision by clinical team members. Fidelity monitoring will be undertaken by a team of trained data collection assistants who have been heavily involved in the intervention development stage and will be highly familiar with the implementation protocol. Fidelity monitoring reports will be discussed frequently with the research manager to identify needs for lay counsellor action/support or intervention modification (see WP5).

We have established preliminary feasibility indicators for each intervention, which will be updated when interventions are finalised. Feasibility indicators which will be common across WP1–4 interventions are: meeting recruitment and retention rates, delivery as intended, measure completion and no significant adverse effects. We will adopt a ‘traffic light’ system for recruitment and retention as follows: red—if rates below 50% (say) then will not proceed; amber—if rates 50%–65% then proceed if there are plans to improve; green—above 65% proceed to definitive trial. Mixed-methods process and evaluation data will be secured for all interventions from adolescents, teachers, parents and lay counsellors to explore: perceived usefulness of the interventions; implementation challenges; unintended negative effects; safeguarding challenges; the process of change and intervention development needs. Evaluation outcomes will inform intervention improvements and parameters for a definitive trial.

### Sample size calculation

The planned sample for the feasibility study by intervention is detailed in table 2. The minimum recommended sample size for a feasibility study is 30.^49^ The smallest group of participants are teachers (for the WP2 intervention). To secure a sample of 30, we will need to recruit a minimum of 8 schools, from which we will then be able to recruit approximately n=960 grade 9 adolescents (for WP1 intervention). Given this adolescent sample size, we have been able to calculate power in relation to WP1, where a key aim is to test two candidate primary outcomes measures—the Strengths and Difficulties Questionnaire (SDQ)^50^ and the Revised Child Anxiety and Depression Scale (RCADS).^51^ SDQ is an emotional and behavioural screening tool, culturally validated in India and used widely in adolescent mental health research. RCADS measures anxiety and depression and demonstrates excellent sensitivity to change. A translated RCADS has been used with Indian populations^52^ but full cultural validity needs to be established. As this will be an important tool to strengthen Indian mental health research, we will conduct a full validation study in parallel to the codesign stage. We have determined via a UK school feasibility trial^53^ that the change in SDQ had a SD of 2.8 points. Assuming 80% recruitment, comparing the mean changes in SDQ from 480 participants from the intervention group with 288 from the waitlist group using a 1% significance level has more than 98% power to detect a difference of 1 point on the SDQ Scale. Around 960 adolescents will be approached for WP1. At 65% recruitment, the power remains over 95%. This calculation is based on an analysis of variance approach, that is, regressing the change in SDQ on the intervention status (intervention or waiting list). The power achieved from an analysis of covariance approach, which regresses the final SDQ Score on baseline and intervention status, should be similar. Should the mechanism of the WP1 intervention be similar across population subgroups, we can therefore show good power. There may, however, be differences in the operation of the intervention between subgroups, such as government versus private schools. In that case, assuming an even division of samples, the power becomes 85% with 80% recruitment and 78% with 65% recruitment. A significance level of 1% is used rather than 5% since the sensitivity of the outcome measures is sought to be compared—that is, the SDQ will be compared in sensitivity in this setting with the RCADS.

**Table 2 T2:** Planned sample size for each intervention in the feasibility study

WP	Intervention	N	Sample
1	Universal curriculum adolescent mental health programme	960	Grade 9 15–16 year olds from 8 schools (120 per school)
2	Teacher education programme	32	Grade 9 teachers (4 per school)
3	School climate intervention	8 schools	To be defined following intervention selection
4	Parental mental literacy intervention	960 sets of parents	Aim to reach all parents/carers of WP1 participants

WP, work packages.

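### The WP1 power claims (over 98% and over 95%) count pupils as independent, but eight whole schools are randomised 5:3, so the design does not have that power

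*Protocol article*

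**What the plan says.** Under Year 2: feasibility testing, allocation is by school: "The feasibility study will run in eight schools, with three randomly assigned to waitlist". Table 2 plans 120 grade 9 pupils in each of the eight schools, 960 in all.

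The Sample size calculation section then works in pupils. From an earlier UK school feasibility trial it takes that "the change in SDQ had a SD of 2.8 points". At 80% recruitment it describes "comparing the mean changes in SDQ from 480 participants from the intervention group with 288 from the waitlist group" and states that this, "using a 1% significance level has more than 98% power to detect a difference of 1 point on the SDQ Scale". It adds: "At 65% recruitment, the power remains over 95" per cent. The model behind the figures is a regression of SDQ change on trial arm alone. An ANCOVA is said to give similar power, and the section concludes that power is good if the intervention works similarly across subgroups.

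Under Data analysis plan (WP1–5: feasibility study), school effects are treated as fixed. The supporting mixed model has two levels, timepoints within participants, and no school level.

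**The concern.** When schools are randomised, the variance of the arm difference includes variation between schools, and the information about that variation comes from eight units, not 768 pupils. A calculation that uses 480 and 288 as independent observations leaves this out and overstates power.

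The consequences run both ways:

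- A reader who believes the 98% figure will take a non-significant SDQ result as good evidence against a 1-point effect. If true power is nearer 14% to 47%, it is not.
- A significant result from an analysis that treats pupils as independent may reflect which schools fell in which arm rather than the intervention.

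The calculation also assumes no loss by the 3-month outcome, although the article's own traffic-light rule rates any retention above 65% as green.

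**Working it through.** **Inputs from the article.** Difference 1 point; SD of change 2.8; significance level 1% (sidedness not stated; two-sided used here); 480 vs 288 at 80% recruitment, i.e. 5 × 96 and 3 × 96; 390 vs 234 at 65% recruitment, i.e. 5 × 78 and 3 × 78; eight schools, 5:3.

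**Assumed.** The ICC of SDQ change, which the article does not give: 0 to 0.05. Total SD is held at 2.8 and school sizes are taken as equal.

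**1. Reproducing the stated power (independent pupils).**

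SE = 2.8 × √(1/n₁ + 1/n₂); power ≈ Φ(1/SE − 2.576).

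- 480 vs 288: SE = 0.209, 1/SE = 4.79, power 98.7% (t-test 98.6%).
- 390 vs 234: SE = 0.232, 1/SE = 4.32, power 95.9% (t-test 95.8%).

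Both match the article with no inflation at all, so clustering did not enter.

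**2. Allowing for school allocation.**

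Design effect DE = 1 + (m − 1) × ICC; SE = 2.8 × √[(DE/m) × (1/5 + 1/3)]. Power is given for a normal test and for a t-test on 8 − 2 = 6 df (noncentral t; two-sided 1% critical value 3.71). The 95% CI half-width is 2.447 × SE.

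At 80% recruitment (m = 96):

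| ICC | DE | SE | Power, normal | Power, 6 df | 95% half-width (points) |
|---|---|---|---|---|---|
| 0 | 1.00 | 0.209 | 98.7% | 80% | 0.51 |
| 0.005 | 1.48 | 0.253 | 91.5% | 61% | 0.62 |
| 0.01 | 1.95 | 0.291 | 80% | 47% | 0.71 |
| 0.02 | 2.90 | 0.355 | 59% | 31% | 0.87 |
| 0.05 | 5.75 | 0.500 | 28% | 14% | 1.22 |

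At 65% recruitment (m = 78), 6-df power is 71%, 54%, 42%, 28% and 13% at the same ICCs.

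**3. How much is due to the 1% level.** With 6 df and a 5% level at m = 96, power is 81%, 65% and 39% at ICCs of 0.01, 0.02 and 0.05. The strict level costs a good deal, but the claimed power is not recovered at 5% either.

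**4. Attainable p-value.** Drawing 3 of 8 schools without restriction gives C(8,3) = 56 allocations, so an exact randomisation test cannot give p below 1/56 = 0.018. On that basis the 1% level cannot be reached whatever the effect. Stratifying the draw would leave fewer allocations and raise that floor.

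**5. Error rate if pupils are analysed as independent.** The true level of a nominal two-sided 1% test is 2 × [1 − Φ(2.576/√DE)]: 6.5% at ICC 0.01, 13% at 0.02 and 28% at 0.05 (m = 96).

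**6. Whether fixed school effects help.** They do not. Each school is in one arm only, so arm is a linear combination of the school indicators and cannot be estimated separately beside a full set of them. Fixing the school effects also keeps between-school variation out of the standard error.

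**7. Retention alone, ignoring clustering.** 65% recruitment followed by 65% retention leaves about 390 × 0.65 = 254 and 234 × 0.65 = 152. SE = 0.287, 1/SE = 3.48, power about 81% (t-test), not over 95%.

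**The case against.** The best defence is that power did not set the sample. Eight schools follow from the teacher target of 30, and the power for pupils was worked out afterwards. The progression indicators concern recruitment, retention, delivery, measure completion and adverse effects, and none is an SDQ p-value. That is right, and it is why no extra schools are asked for. But the article still publishes the power as a property of this design and concludes that it is good, and that is not so.

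Other points deserve weight:

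- **The ICC is assumed.** The size of the shortfall depends on it; at 0.005 the normal-test figure is still 91.5%. The direction does not depend on it: any positive ICC lowers power, and 6 df alone takes it to 80%.
- **A null result would not always be uninformative.** With half-widths of 0.71 and 0.87 points, an estimate close to zero would exclude a 1-point effect at ICCs of 0.01 and 0.02, but not at 0.05. Non-significance at 1% would still say little by itself.
- **No randomisation test is planned.** The 1/56 limit is supporting evidence; the main case rests on the 6-df figures.
- **The retention example is a boundary case.** It takes 65% on both criteria, and exactly 65% falls in amber. The article's 65% recruitment scenario also equals 80% recruitment with about 81% retention (624/768), so moderate loss is partly covered.
- **The arithmetic itself is correct.** The fault is the independence assumption behind it.

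**Conclusion.** The concern holds. The stated powers are correct for individually randomised pupils and wrong for the school-randomised design that the article describes. At 80% recruitment and a two-sided 1% level, a test that respects the eight schools has 80% power at best (ICC of zero), and 47% to 14% over assumed ICCs of 0.01 to 0.05; at 65% recruitment the range is 42% to 13%. These figures rest on the article's SD of 2.8, equal school sizes, full retention among those recruited and the assumed ICCs. That the power is overstated does not depend on the ICC chosen. Because the figure is published as a strength of the design and is not true of it, it must be corrected, even though it did not determine the number of schools.

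**What to change.** In the Sample size calculation section:

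1. Delete the claims of more than 98% and over 95% power, and the conclusion that power is good.
2. State the expected precision of the arm difference in SDQ change with eight schools split 5:3, over ICCs of 0.01 to 0.05 and with stated retention. Before any loss to follow-up, the 95% half-width at 80% recruitment is about 0.7 to 1.2 points.
3. Say that the SDQ comparison is for estimation, to plan the definitive trial: the effect, the SD of change, and the ICC with its confidence interval. It is not a test at the 1% level. The comparison of SDQ and RCADS sensitivity can be kept and reported in the same way, as estimates with intervals.

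The cost is a rewritten paragraph with less favourable figures. No extra schools are needed.
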